Furthermore, because the subendocardial layer is the first to be affected in AS, the longitudinal alignment of myocardial fibers in this layer causes decreased longitudinal contraction, an early sign of LV dysfunction. There are data showing, that global longitudinal strain (GLS) correlate with LV myocardial fibrosis and is a predictor of adverse events in patients with severe AS [16, 17].

Novel diagnostic strategies and more accurate evaluation of the disease severity and consequences of AS are needed in the assessment of subclinical myocardial dysfunction and the detection of myocardial fibrosis to challenge current recommendations for the timing of AVR. To date there are limited data on simultaneous assessment of diffuse myocardial fibrosis by noninvasive multimodality imaging and histological confirmation in severe AS. Optimal T1 mapping application also remains unclear, and data assessing its prognostic value in severe AS are still lacking. Our multicenter prospective trial aims to: (i) non-invasively assess myocardial fibrosis and validate it against histological data in patients undergoing surgical AVR and (ii) assess the impact of myocardial fibrosis on clinical outcomes following AVR in both surgical and TAVR cohorts.

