#### T1 mapping

The present study describes image acquisition parameters by focusing on T1 mapping images, which will be acquired in four-chamber long-axis and short-axis (at the basal and midventricular levels) images before and at 15 min after contrast administration. All T1 mapping images have been acquired using modified Look-Locker inversion-recovery (MOLLI) [30, 31] using the Motion Correction technique (on the Siemens scanner). The following readout parameters will be used: slice thickness: 8 mm; flip angle: 35; field of view: 384 × 327; effective TI: 193 ms; voxel size: 1.5 × 1.5 × 8 mm; TR/TE: 312.64/1.33 ms; partial Fourier: 7/8; and parallel imaging factor: 2 (VUH) and slice thickness 8 mm, flip angle 35, matrix size 256 × 256, inversion time 130 ms, and FOV 380 mm (AAUH).

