#### Measurement of the ECV and native T1 values

The T1 maps will be generated from the CMR workstation after in-line motion correction just after image acquisition (Siemens scanner) or in post-processing software (GE scanner). Two blinded reviewers will independently review all T1 mapping sequences. Regions of interest will be drawn manually in the blood and septum at the midventricular level on the short-axis image, excluding the myocardium with LGE for T1 measurements [13, 32]. Regions of interest in the septum are chosen for myocardial T1, because this area corresponds to the site of myocardial biopsy. The regions of interest will be drawn on the compact myocardium, and the border of the myocardium will not be included. To measure the T1 value of blood, circular regions of interest will be positioned in the LV cavity, avoiding papillary muscle **(**Fig. 2**).**

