**Fig. 2 Fig2:**
[figure not shown]
CMR T1 assessment. To measure the T1 value, regions of interest will be drawn manually in the blood and septum at the midventricular level on the short-axis, avoiding papillary muscle

The ECV of the myocardium will be calculated as follows: ECV% = (ΔR1m/ΔR1b) x (1 - hematocrit level) × 100, where R1 is 1/T1, R1m is R1 in the myocardium, R1b is R1 in the blood, and ΔR1 is the change in relaxivity. The change in relaxivity (ΔR1) was determined using the following equation: ΔR1 = R1post - R1pre, where R1post and R1pre are the R1 after and before gadolinium chelate administration, respectively [33]. Blood samples will be taken on the day of CMR scanning to determine hematocrit and creatinine concentration. Interobserver agreement between 2 different experienced observers will be assessed on different days for 10 randomly selected patients. Figure 3 summarizes the CMR sequences used in this study.

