### Histological analysis

In patients undergoing surgical AVR biopsy specimens will be obtained under direct vision by the surgical team using a surgical scalpel from the basal anteroseptum just after removal of the diseased aortic valve. All myocardium tissue samples will be fixed in 10% neutral buffered formalin and embedded in paraffin. Sections of 3-μm thickness will be made on a Leica RM2145 microtome and stained by hematoxylin and eosin, Masson‘s trichrome, and Congo red methods. Digital images will be captured by using the Aperio Scan-Scope XT Slide Scanner (Aperio Technologies, Vista, CA, USA) under 20× objective magnification (0.5-μm resolution). Histological slides (typically measuring 20–30 sq./mm) will be processed for evaluation of myocardial fibrosis. An experienced (> 25 years of experience) histologist ([name]) blinded to the clinical and CMR data will investigate all biopsy specimens. The fraction of myocardial volume occupied by collagen tissue (collagen volume fraction) will be determined by quantitative morphometry with an automated image analysis system (HALO™) in sections stained with Masson’s trichrome. Quantification of the myocardial fibrosis area will be performed using HALO™ Classifier Module and HALO™ Area Quantification v1.0 algorithms (IndicaLabs, NM, USA) within manually selected regions of interest enclosing the tissue section and excluding endocardium from the analysis. All study assessments are summarized in Table 2**.**

**Table 2 Tab2:** Study assessments

Demographic data and comorbidities	
STS risk score	
EuroSCORE II	
Serum biomarkers:	
▸ Brain natriuretic peptide	
▸ Troponin I	
Cardiovascular imaging biomarkers:	
▸ Transthoracic 2D echocardiogram with strain analysis (GLS)	
▸ 1.5 T contrast-enhanced CMR with T1 mapping (Native T1, ECV)	
Myocardial histological analysis:	
▸Quantitative myocardial fibrosis assessment (CVF)	
Functional status and quality of life assessment:	
▸New York Heart Association functional class	
▸Minnesota Living with Heart Failure Questionnaire	
▸6-min walking test	

Abbreviations: 2D- two-dimensional, ECV- extracellular volume, EuroSCORE- European System for Cardiac Operative Risk Evaluation, CMR- cardiovascular magnetic resonance, CVF- collagen volume fraction, GLS- global longitudinal strain, STS- Society of Thoracic Surgeons

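### The T1/ECV region of interest is justified as matching the biopsy site, but it matches in wall only: the region is mid-ventricular septum and the biopsy is basal anteroseptum

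*Protocol article*

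**What the plan says.** Under Measurement of the ECV and native T1 values, the protocol article fixes the measurement site: "Regions of interest will be drawn manually in the blood and septum at the midventricular level on the short-axis image, excluding the myocardium with LGE". It then explains the choice of wall: "Regions of interest in the septum are chosen for myocardial T1, because this area corresponds to the site of myocardial biopsy". The Fig. 2 legend repeats the level: "regions of interest will be drawn manually in the blood and septum at the midventricular level on the short-axis, avoiding papillary muscle".

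Histological analysis says that the surgical team obtains the specimen "from the basal anteroseptum just after removal of the diseased aortic valve". Collagen volume fraction (CVF) is then quantified "within manually selected regions of interest enclosing the tissue section and excluding endocardium from the analysis".

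T1 mapping lists the maps acquired: a four-chamber view and "short-axis (at the basal and midventricular levels) images before and at 15 min after contrast administration".

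The last paragraph of Background states aim (i): "non-invasively assess myocardial fibrosis and validate it against histological data in patients undergoing surgical AVR". Statistical analysis serves this aim with Pearson or Spearman correlations of native T1, ECV and GLS with histological fibrosis, stepwise regression for the degree of fibrosis, and comparisons of imaging data between groups defined by histology. Study population plans 60 surgical patients, the only ones with a biopsy.

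**The concern.** The protocol sets its own criterion for the imaging site, which is correspondence with the biopsy, and then meets it only in part. The imaging value comes from one level of the septum and the tissue from another. A basal map that would allow a level-matched value is acquired before and after contrast, but the article names no region of interest on it.

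Aim (i) is at stake. If fibrosis differs between the two levels, regional difference is added to the measurement error in the CMR-histology comparison. A weak correlation could then partly reflect where the measurement was taken and not only how well T1 mapping reflects collagen. Strengths presents the histological validation as an asset of the study, and Limitations does not mention the difference in level.

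**Working it through.** The article states no expected CMR-histology correlation and no power for it, so there is no planned figure to reproduce. The check is a comparison of the text, followed by a test of whether any size can be derived.

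**1. The two sites side by side**

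| | CMR region of interest | Biopsy |
|---|---|---|
| Wall | septum | septum (anterior part) |
| Level | mid-ventricular | basal |
| Anterior part only? | not stated | yes |
| Focal scar | myocardium with LGE excluded | no exclusion stated |
| Source | Measurement of the ECV and native T1 values; Fig. 2 legend | Histological analysis |

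The wall agrees and the level does not. The mid-ventricular level appears in both the text and the legend, so a single slip of wording is unlikely. The last difference, in the handling of focal scar, is separate from level and would remain after level matching.

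**2. Is a level-matched value available?** Yes. The basal short-axis map is acquired both before and after contrast. The ECV formula in the article needs only pre- and post-contrast T1 in myocardium and blood, plus the hematocrit taken on the day of the scan. No new scan or blood sample is required.

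**3. Can the effect on the correlation be derived?** Take a simple model. Let k be the correlation between true fibrosis at the mid-septal and the basal anteroseptal site. Let R_mid, R_bas and R_CVF be the reliabilities of the two imaging values and of CVF, with errors independent. Then:

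- basal imaging against CVF: r_bas = sqrt(R_bas × R_CVF)
- mid-septal imaging against CVF: r_mid = k × sqrt(R_mid × R_CVF)
- ratio: r_mid / r_bas = k × sqrt(R_mid / R_bas)

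Three things follow.

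- With equal reliabilities the ratio is k. If fibrosis is uniform along the septum, k = 1 and nothing is lost. If k is below 1, the mid-septal correlation is attenuated.
- If the basal value is noisier (R_bas below R_mid), the ratio rises and can reach or exceed 1 even with k below 1.
- The factor k is a correlation of fibrosis between sites, not of measured ECV between sites. Suppose that both ECV values and CVF reflect one patient-level burden, with independent noise of equal size in the two ECV values. The two ECV values then correlate below 1 because of noise alone, yet each has the same correlation with CVF. A between-site ECV correlation below 1 is therefore compatible with no attenuation.

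The documents give none of k, R_mid, R_bas and R_CVF. The direction is conditional, and the size cannot be derived.

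**4. Which analyses depend on the pairing?** The correlation of native T1 and ECV with histology, the regressions for degree of fibrosis that use them, and their comparison across histological groups. GLS is an echocardiographic measure and does not use this region of interest. The Cox model for the composite outcome uses imaging values without the biopsy, and the sample size rests on a hazard ratio for ECV. Neither changes.

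**The case against.** The strongest reply is that the rationale sentence defends the choice of wall, and on that it is right: the biopsy is septal. The level comes from the sentence before it, which has its own citations, so the protocol does not expressly offer the biopsy as its reason for the mid-ventricular slice. This stands, and it narrows the point to level and to the anterior part of the septum. The sentence still claims a correspondence with the biopsy site that is incomplete.

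A reader might infer that the correlation is biased low, or attach a percentage loss to it. The documents do not support either. They say nothing about variation between basal and mid septum, the target is diffuse fibrosis, and myocardium with LGE is excluded from the region, so uniformity cannot be ruled out.

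A reader might also infer that the basal map goes unused. That rests on silence in a condensed article, which also says that two reviewers look at all T1 mapping sequences. What can be said is that the only region of interest described is mid-ventricular.

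Finally, a basal region is not free of problems. Partial volume near the outflow tract could make it noisier, and an 8-mm slice will never match a small histological section. This stands too, and it is why both sites should be reported instead of replacing one with the other.

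**Conclusion.** The mismatch in level is certain from the text: the imaging region is mid-ventricular septum, not limited to its anterior part, and the biopsy is basal anteroseptum. The consequence is conditional. If fibrosis varies along the septum, the CMR-histology correlation may be attenuated; if diffuse fibrosis is uniform there, the loss may be negligible. No numerical range is justified.

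Severity is moderate. The point affects aim (i) in surgical patients, and that validation is not among the primary or secondary items under Study objectives. It would be wrong to infer a threat to the primary result: the composite outcome, its Cox analysis and the total of 110 patients do not depend on where the biopsy was cut. Because the basal maps are part of the planned acquisition, the matched measurement remains possible. It should be specified before the correlations are examined, so that the choice of site cannot follow the results.

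**What to change.** - For the histological validation in surgical patients, pre-specify an additional region of interest in the anteroseptal segment of the basal short-axis native and post-contrast maps.
- Report the correlation of native T1 and ECV with CVF for both the basal anteroseptal and the mid-septal values, whatever they show.
- Keep the mid-septal region for the prognostic analyses.
- Correct the rationale sentence to say that the mid-septal region shares the wall of the biopsy but not its level. If the basal region is not added, list the difference under Limitations.

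The cost is one extra region per surgical patient (60 planned), drawn by the same blinded readers on existing maps, with no new scan, contrast or visit. The downside is possible partial volume near the outflow tract, which is covered by showing the mid-septal result beside the basal one.

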**Fig. 2 Fig2:**
[figure not shown]
CMR T1 assessment. To measure the T1 value, regions of interest will be drawn manually in the blood and septum at the midventricular level on the short-axis, avoiding papillary muscle

The ECV of the myocardium will be calculated as follows: ECV% = (ΔR1m/ΔR1b) x (1 - hematocrit level) × 100, where R1 is 1/T1, R1m is R1 in the myocardium, R1b is R1 in the blood, and ΔR1 is the change in relaxivity. The change in relaxivity (ΔR1) was determined using the following equation: ΔR1 = R1post - R1pre, where R1post and R1pre are the R1 after and before gadolinium chelate administration, respectively [33]. Blood samples will be taken on the day of CMR scanning to determine hematocrit and creatinine concentration. Interobserver agreement between 2 different experienced observers will be assessed on different days for 10 randomly selected patients. Figure 3 summarizes the CMR sequences used in this study.

**Fig. 3 Fig3:**
[figure not shown]
CMR protocol for FIB-AS study

### Histological analysis

In patients undergoing surgical AVR biopsy specimens will be obtained under direct vision by the surgical team using a surgical scalpel from the basal anteroseptum just after removal of the diseased aortic valve. All myocardium tissue samples will be fixed in 10% neutral buffered formalin and embedded in paraffin. Sections of 3-μm thickness will be made on a Leica RM2145 microtome and stained by hematoxylin and eosin, Masson‘s trichrome, and Congo red methods. Digital images will be captured by using the Aperio Scan-Scope XT Slide Scanner (Aperio Technologies, Vista, CA, USA) under 20× objective magnification (0.5-μm resolution). Histological slides (typically measuring 20–30 sq./mm) will be processed for evaluation of myocardial fibrosis. An experienced (> 25 years of experience) histologist ([name]) blinded to the clinical and CMR data will investigate all biopsy specimens. The fraction of myocardial volume occupied by collagen tissue (collagen volume fraction) will be determined by quantitative morphometry with an automated image analysis system (HALO™) in sections stained with Masson’s trichrome. Quantification of the myocardial fibrosis area will be performed using HALO™ Classifier Module and HALO™ Area Quantification v1.0 algorithms (IndicaLabs, NM, USA) within manually selected regions of interest enclosing the tissue section and excluding endocardium from the analysis. All study assessments are summarized in Table 2**.**

**Table 2 Tab2:** Study assessments

Demographic data and comorbidities	
STS risk score	
EuroSCORE II	
Serum biomarkers:	
▸ Brain natriuretic peptide	
▸ Troponin I	
Cardiovascular imaging biomarkers:	
▸ Transthoracic 2D echocardiogram with strain analysis (GLS)	
▸ 1.5 T contrast-enhanced CMR with T1 mapping (Native T1, ECV)	
Myocardial histological analysis:	
▸Quantitative myocardial fibrosis assessment (CVF)	
Functional status and quality of life assessment:	
▸New York Heart Association functional class	
▸Minnesota Living with Heart Failure Questionnaire	
▸6-min walking test	

Abbreviations: 2D- two-dimensional, ECV- extracellular volume, EuroSCORE- European System for Cardiac Operative Risk Evaluation, CMR- cardiovascular magnetic resonance, CVF- collagen volume fraction, GLS- global longitudinal strain, STS- Society of Thoracic Surgeons

### Outcome measures

Primary outcome measure: a composite of all-cause mortality and MACEs (time frame: from 30 days up to 24 months following AVR).

Secondary outcomes measures:
In-hospital and 30-day all-cause mortality (time frame: 30 days)Length of hospital stayTime to the event (death or MACE) (time frame: 24 months)Cardiovascular mortality (from 30 days up to 24 months following AVR)

Primary outcome endpoints will be defined according to current guidelines: Valve Academic Research Consortium-2 (VARC-2) definitions [34] and guidelines for reporting mortality and morbidity after cardiac valve interventions [35]. Cardiovascular mortality defined as: (1) death due to proximate cardiac cause (e.g., myocardial infarction, cardiac tamponade, worsening heart failure, and low cardiac output syndrome); (2) death caused by non-coronary vascular conditions (e.g., pulmonary embolism, stroke, aortic rupture, or vascular dissection); (3) all procedure-related deaths; (4) all valve-related deaths; and (5) sudden or unwitnessed death [35]. All-cause mortality defined as the sum of cardiovascular and non-cardiovascular deaths, with the latter defined as any death in which the primary cause is clearly related to other than cardiovascular condition. 30-day mortality defined as death occurring within 30 days or during index procedure hospitalization, if the postoperative length of stay is longer than 30 days.

### Clinical follow-up

Patients will be routinely followed and managed according to available guidelines. Clinical outcome data will be collected from patient clinical visits at 3, 12, and 24 months following AVR. Serum biomarker analysis and 2D echocardiography with STE analysis will be performed at each follow-up visit. A second CMR scan will be performed 1 year after AVR. The 6MWT will be performed, and the MLHF questionnaire will be administered at the 12-month follow-up visit. FIB-AS study follows the standard protocol items: recommendation for interventional trials (SPIRIT) guidelines [36]. The study timeline is presented in Fig. 4**.**

**Fig. 4 Fig4:**
[figure not shown]
Standard protocol items: recommendation for interventional trials (SPIRIT) figure of participant timeline. Abbreviations: 2D- two-dimensional, 6MWT- 6-min walking test, CMR- cardiovascular magnetic resonance, MACEs- major adverse cardiovascular events, m- months, MLHFQ- Minnesota Living with Heart Failure Questionnaire. *Endomyocardial biopsy will be performed only in patients undergoing surgical AVR

### Statistical analysis

Linear regression analysis to model the relationship between the extent of myocardial fibrosis and patient outcomes.Univariate and multivariate regression analysis of CMR-derived predictors of adverse clinical events.Comparison of clinical, serum, and imaging (CMR and echocardiography) biomarker data between patients with different extents of fibrosis.

The statistical analysis will be performed under the supervision of [name] at the Institute of Applied Mathematics, Vilnius University Faculty of Mathematics and Informatics. Descriptive statistics will be used to summarize the demographic, clinical, and imaging data characteristics of each patient. Categorical variables will be presented as the frequency and percentage, and continuous variables will be expressed as the mean and standard deviation or median and interquartile range. The 95% confidence interval will be reported for primary outcomes. Patients will be grouped, depending on the presence and extent of histologically measured myocardial fibrosis, and their clinical and imaging data will be compared for significant differences. Bivariate correlation analysis of the native T1, ECV, and GLS values with the degree of histologically measured myocardial fibrosis will be performed. Pearson or Spearman correlation coefficient will be used as the measure of correlation. To identify independent predictors of the degree of myocardial fibrosis, multivariate stepwise regression analysis will be performed separately for native T1, ECV, and GLS values, along with demographic and clinical data. The composite event will be assessed from a simple Cox model for survival analysis using ECV, native T1, and GLS, and their c-indexes will be compared for how well each marker predicts the clinical outcome. In addition, the Kaplan–Meier method will be used for the cumulative survival analysis with log-rank test to assess statistical differences between the curves of patients with different degree of myocardial fibrosis. A two-tailed *p*-value of < 0.05 will be considered statistically significant. The statistical analysis will be performed using the R language and environment for statistical computing (version 3.5.1) [37].

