### Study population

We will recruit patients with severe AS requiring AVR according to current treatment recommendations [19]. We will exclude patients with obstructive coronary artery disease requiring revascularization or other significant valvular pathology. The inclusion and exclusion criteria are set in Table 1**.** The recruitment period will be 24 months, from May 2019 to May 2021. We expect to enroll a total of 110 patients: 60 patients undergoing surgical AVR and 50 patients undergoing TAVR.

**Table 1 Tab1:** Inclusion and exclusion criteria

Inclusion Criteria:	
• Severe AS (defined as AVA ≤1 cm^2^ or AVA index (iAVA) ≤0.6 cm^2^/m^2^ as determined by ultrasound examination)	
• Males and females of any ethnic group ≥18 years of age	
• Signed an informed patient consent form	
Exclusion Criteria:	
• Unable to provide informed consent	
• Severe valvular heart disease other than AS	
• Coronary artery disease requiring revascularization	
• History of myocardial infarction	
• Prior cardiac surgery	
• Severe renal impairment - eGFR < 30 ml/min/1.73 m^2^	
• Any absolute contraindication to CMR	
• Permanent atrial fibrillation	
• Patient with implanted cardiac devices (pacemaker, ICD)	
• Inherited or acquired cardiomyopathy	
• Other medical conditions that limit life expectancy or preclude AVR	
• Pregnant or nursing women	
• Mental condition rendering the patient unable to understand the nature, scope, and possible consequences of the study or to follow the protocol	

Abbreviations: AS- aortic stenosis, AVA- aortic valve area, iAVA- aortic valve area index, AVR- aortic valve replacement, CMR- cardiovascular magnetic resonance, eGFR- estimated glomerular filtration rate, ICD- implantable cardioverter defibrillator

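### Stepwise selection in about 60 biopsied patients does not support a claim of independent predictors of fibrosis; a loose linear-regression line also needs reconciling with the Cox plan

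*Protocol article*

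**What the plan says.** The stepwise plan is in the protocol article, Statistical analysis. Its purpose is stated as "To identify independent predictors of the degree of myocardial fibrosis", and the method is that "multivariate stepwise regression analysis will be performed separately for native T1, ECV, and GLS values, along with demographic and clinical data". The preceding sentences concern histologically measured fibrosis, so histology is the implied response. No candidate list or rule for entry and removal is given.

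The number of patients follows from other sections. Study design restricts the biopsy to surgical patients, and Study population expects "60 patients undergoing surgical AVR and 50 patients undergoing TAVR". The section on speckle tracking limits strain analysis to the Vilnius site. The GLS model can therefore use only biopsied Vilnius patients, whose number is not stated.

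The same section opens its list of analyses with "Linear regression analysis to model the relationship between the extent of myocardial fibrosis and patient outcomes". Outcome measures gives "Primary outcome measure: a composite of all-cause mortality and MACEs (time frame: from 30 days up to 24 months following AVR" and, among the secondary outcomes, "In-hospital and 30-day all-cause mortality (time frame: 30 days", length of stay, time to death or MACE, and cardiovascular mortality. Statistical analysis later says "The composite event will be assessed from a simple Cox model for survival analysis using ECV, native T1, and GLS", and adds that "the Kaplan–Meier method will be used for the cumulative survival analysis with log-rank test".

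**The concern.** Stepwise selection uses the same data to choose the covariates and to test them. With about 60 patients and an open candidate list, the final model's p-values, coefficients and R² look better than they are. A noise covariate can be reported as an independent predictor. If the imaging marker competes for entry like any other variable, it can drop out, and its adjusted relation to collagen volume fraction then goes unreported. This bears on the first stated aim, validation of imaging against histology, which the article also lists among its strengths.

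The linear-regression line is a lesser matter. Read literally, it covers events and censored times, for which the section already names Cox. Two methods would then address fibrosis against the composite, with nothing to say which governs.

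**Working it through.** **Plan's own figure.** None is stated for the stepwise or linear regressions. The only sized analysis is the Cox model for the composite (Sample size justification: hazard ratio 1.32, power 0.8, 100 evaluable patients), and it does not bear on the stepwise models.

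**Stepwise, no true predictor.** Inputs from the documents: 60 surgical patients expected; two-sided 0.05. Assumptions: 5 to 20 independent candidates, none related to fibrosis; n = 60, 54 (10% fewer) or 40 (an illustration for single-site GLS). P-value selection enters at 0.05 and removes at 0.10. There were 600 runs per cell, so the simulation standard error is at most √(0.25/600) = 0.020. The percentages are runs with at least one significant covariate in the final model.

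| Candidates k | p-value rule, n=60 | n=54 | n=40 | AIC rule, n=60 | No selection, 1−0.95^k |
|---|---|---|---|---|---|
| 5 | 23% | 25% | 23% | 24% | 23% |
| 10 | 44% | 42% | 38% | 52% | 40% |
| 15 | 59% | 54% | 54% | 68% | 54% |
| 20 | 63% | 66% | 61% | 82% | 64% |

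The last column matters. Under the p-value rule most of the false-positive rate is multiplicity over an open candidate list. AIC selection adds to it, for example 52% against 40%.

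**Optimism due to selection itself.** At n = 60 the AIC models kept on average 0.93, 2.02, 3.45 and 4.88 noise terms for k = 5, 10, 15 and 20, with mean apparent R² of 0.053, 0.112, 0.178 and 0.234. Per kept term that is 0.053/0.93 = 0.057, 0.112/2.02 = 0.055, 0.178/3.45 = 0.052 and 0.234/4.88 = 0.048. A noise term fixed in advance has expected R² of 1/(n−1) = 1/59 = 0.017, so selected noise terms look about three times as informative. At n = 40 the mean apparent R² was 0.081, 0.170, 0.281 and 0.403.

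**Stepwise with weak true effects.** Assumptions: n = 60, 10 candidates with pairwise correlation 0.3, true coefficients 0.30 and 0.20, the rest zero, p-value rule, 1,000 runs. The stronger true predictor was selected in 56.5% of runs, so it was lost in 43.5%. When selected, its mean coefficient was 0.41 against 0.30. Part of the excess arises when the correlated second predictor is left out (0.20 × 0.3 = 0.06 where it is the only other term); the rest is selection. A noise variable entered in 37% of runs. If the imaging marker were that predictor and were not forced in, it would be unreported in over four runs in ten.

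**Linear-regression line.** The listed outcomes are a composite event, deaths, a time to event and length of stay. Only length of stay is continuous, and it is skewed. To see what literal use on events would do, assume ECV SD 2 to 3 and 24-month event risk 15% to 30%:
- With everyone followed to 24 months, the slope on observed time equals the restricted-mean slope (for example −0.478 months per ECV point for both, at SD 3 and 15%).
- With uniform censoring over 0 to 24 months, it falls to −0.162, and 0.162/0.478 = 34%; across the four settings the range is 34% to 36%. This is far heavier censoring than the 10% loss the article expects.
- A linear model for the event indicator gives negative fitted risks for about 1% to 9% of patients.

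**The case against.** Five points can be made for the plan.

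- **The missing detail may be elsewhere.** A fuller protocol or SAP may list the candidates and the selection rule. That is fair, and their absence is not the point. The article positively names stepwise selection and the claim it should support. A list would fix the place within the range above but would not remove the optimism.
- **The false-positive rates are largely multiplicity.** This stands. A reader might take the whole 23% to 63% as harm done by the stepwise algorithm. A fixed model with the same number of covariates, each tested at 0.05, would flag noise about as often. What belongs to selection is the inflated coefficient and R², the extra false positives under AIC, and the possible loss of the marker.
- **An unselected analysis is also planned.** The section specifies Pearson or Spearman correlations of native T1, ECV and GLS with histological fibrosis. These are untouched, so validation does not depend on the stepwise models alone; only the adjusted claim does.
- **Whether the marker is forced in is not stated.** Running the models separately per marker may imply that it is. Its loss is a possibility, not something the article says will happen.
- **The linear-regression line may mean continuous outcomes.** Adverse clinical events have their own item in the same list. LV remodeling, the walking test and the quality-of-life score suit a linear model, and length of stay is a weak but not invalid use. A reader might infer that the primary result rests on linear regression and is therefore invalid. The documents do not support that: the composite is given to Cox, Kaplan–Meier and log-rank, and the study is sized on Cox.

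**Conclusion.** The stepwise point holds, for a non-primary analysis that serves a stated aim. With about 60 biopsied patients, and fewer for GLS, the planned models cannot support a claim of independent predictors. With no true predictor, at least one significant covariate appears in about 23% to 63% of runs under p-value selection for 5 to 20 candidates. With weak true effects, the selected coefficient averaged 0.41 against 0.30. These sizes rest on the assumed candidate number, selection rule and effects. Sixty is an expected number, not a cap.

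The linear-regression line is a wording conflict to reconcile. It does not put the primary result at risk.

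**What to change.** **Main change.** Replace the stepwise models with one short pre-set linear model per marker:
- Response: collagen volume fraction.
- Covariates: the marker, age and sex, plus site for native T1 and ECV, because the sites use different scanners. Site is constant in the single-site GLS data and must be left out there.
- The marker is forced in, and its adjusted coefficient and partial R² are reported with confidence intervals.
- Any stepwise search is labelled exploratory.

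With 60 patients, the native T1 and ECV models estimate four slopes and an intercept, leaving 60 − 5 = 55 residual degrees of freedom.

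**Secondary change.** Limit the opening linear-regression line to named continuous outcomes: LV remodeling, the 6-minute walking test, the Minnesota questionnaire, and length of stay on a log scale. Keep Cox for the composite and the other event outcomes.

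**Cost.** Analysis wording only, with no new data. What is lost is a confirmatory, data-driven search for other predictors, which about 60 patients could not support in any case.
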